**Methods/Design:**

Overweight or obese participants will be randomly allocated to one of three conditions: (1) a psycho-education plus an implementation intentions and mental imagery condition; (2) a psycho-education plus an implementation intentions and mental imagery condition with text messages; or (3) a psycho-education control condition. The intervention will be delivered via video presentation to increase the intervention’s applicability in multiple contexts and keep costs low. We hypothesise that the intervention conditions will lead to statistically-significant changes in the primary and secondary outcome variables measured at 6 and 12 weeks post-intervention relative to the psycho-education control condition after controlling for baseline values. The primary outcome variable will be body weight and secondary outcome variables will be biomedical (body mass, body fat percentage, muscle mass, waist-hip circumference ratio, systolic and diastolic blood pressure, low-density lipoprotein, high-density lipoprotein, total cholesterol, triglycerides, blood glucose and insulin levels), psychological (quality of life, motivation, risk perception, outcome expectancy, intention, action self-efficacy, maintenance self-efficacy, goal setting and planning), and behavioural (self-reported diet intake, and physical activity involvement) measures. We also expect the intervention condition augmented with text messages to lead to statistically significant differences in the primary and secondary outcome variables at the follow up periods after controlling for baseline values.

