### Changing health behaviour

For health professionals to support clients to lose weight, it is necessary to identify the factors related to health-related behaviour change and use them as a basis for intervention design [15,16]. These factors are outlined in many different behaviour change models, particularly social psychological models which aim to explain intentional and motivated behaviour that have been applied to predict and understand health behaviour [17]. Researchers seeking behavioural solutions to health-behaviour need to target psychological factors that are considered changeable and malleable to evoke health-behaviour change. These psychological factors can be targeted by sets of behaviour-change techniques that can evoke a change in the psychological factors linked to health behaviours [18,19].

The current intervention adopts the HAPA [5], an integrated social psychological model that has been widely used to identify the components related to changes in weight loss behaviours and how components can be used to inform the intervention content to ensure the change process is clearly identified (see Figure 1). The HAPA states that the process of health behaviour change consists of two phases: a motivational phase that leads an individual to form the intention to change their behaviour, and a volitional phase that leads the individual to performing the actual behaviour [5]. Two strategies that map closely on to the volitional and motivational phases of the HAPA include implementation intentions and mental imagery, respectively. The intervention components are designed to target both the motivational and implemental phases of the HAPA. The components are proposed to lead to optimal behaviour change by providing individuals with the confidence and motivation to engage in the behaviour, as well as the capacity to convert motivation into actual behaviour change [20].

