### Psychological measures

Participants will be instructed to complete the outlined psychological measures before and after viewing the video presentation intervention unless specified otherwise. Variables from the HAPA will be measured to assess the psychological mediators that may explain the effects of the intervention on the behavioural and biomedical outcomes. The HAPA measures include items adapted from Barg and colleagues’ [51] measure of assessing risk perception for developing cancer for physically inactive middle aged adults. *Risk perception* will be assessed using four items on a 6 point Likert scale ranging from 1 (strongly disagree, much lower, not likely) to 6 (don’t know/refused) to measure perceived risk of developing obesity related risk factors. For example, “I think it is likely that I will develop health problems related to obesity at some point in my life.” *Outcome expectancy* will be assessed using six items with responses ranging from 1 (strongly disagree, not at all effective) to 5 (strongly agree, extremely effective) to question participants about the effect of diet and physical activity on health risks related to weight gain. For example, “I think that consuming fewer calories per day is a very important way to help me to lose weight”. *Intention* will be assessed with four items that ask participants how much they plan and intend to follow the diet guidelines and/or to participate in the recommended physical activity amount over the next 12 weeks. Responses range from 1 (strongly disagree) to 5 (strongly agree). For example, “I intend to participate in daily physical activity with a minimum of 30 minutes of planned exercise on each individual occasion over the next 6 weeks. *Action self-efficacy* will be measured using 10 items regarding participants’ confidence and ability to engage in the recommended diet and physical activity guidelines over the next 12 weeks. Prior to answering the questions, participants would have heard the recommendations during the video presentation. Items are on a 5 point Likert scale ranging from 1 (not confident, not likely, strongly disagree) to 5 (completely confident, extremely confident, strongly agree). For example, “if it were entirely up to you, how confident are you that you would be able to follow a diet that requires you to consume fewer calories per day on each individual occasion over the next 6 weeks?” *Maintenance self-efficacy* will be measured using 18 items on a 5 point Likert scale ranging from 1 (not confident) to 5 (completely confident) to measure barriers to engage in the recommended physical activity or diet guidelines. For example, participants were asked “How confident are you that you will do daily physical activity with a minimum of 30 minutes of planned exercise during your leisure time on each individual occasion over the next 6 weeks even if…” followed by a list of barriers, such as, but not limited to bad weather and feeling tired. The participants *planning* will be assessed using two items ranging from 1 (strongly disagree) to 5 (strongly agree) that ask participants if they had made a detailed plan about when, where and how they would engage in physical activity or follow the diet guidelines. For example, “I have made a detailed plan about when, where, and how I will do daily physical activity with a minimum of 30 minutes of planned exercise on each individual occasion over the next 6 weeks”.

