
Further variables that relate to the HAPA were adopted from Hagger and colleagues [32]. *Motivation* will be assessed at baseline by asking participants to respond to six items that question motivation to participate in physical activity and change their diet. For example, “how motivated are you to change your diet on each individual occasion over the next 12 weeks?” Item responses are based on a 6 point Likert scale ranging from 1 (not at all motivated, no effort at all) to 6 (extremely motivated, all my effort). In addition four items exploring engagement in mental imagery exercises will be used. Participants will be asked to indicate the level to which they were able to imagine the task. For example, “to what extent did you visualise in your mind (imagine) exactly how you might reach your diet goals (example, consuming fewer calories per day) on each individual occasion over the next 6 weeks?” The items are on a 6 point Likert scale ranging from 1 (indicating did not imagine), to 6 (indicating clearly imagined).

*Goal setting* will be measured by asking participants six open ended questions. For example, ‘What are your goals for physical activity?’ The answers to these questions will be “coded” appropriately based on whether they are appropriate and realistic. *Intervention checks* will also be included to ensure that participants engaged with and completed the implementation intention and mental imagery exercises appropriately and according to protocol. That is, participants will be asked to record their goals; If-then plans; and a list of the steps they imagined during the intervention process. The answers to these questions will be “coded” appropriately based on whether they are appropriate and realistic. These variables will be measured as they are expected to mediate the key components of the intervention. That is, the effect of the mental imagery component of the intervention variable on the primary and secondary outcomes is expected to mediate the HAPA variables of self-efficacy, motivation, outcome evaluation, and intention. Similarly, the effect of the if-then plan component of the intervention on the primary and secondary outcomes is expected to be mediated by the HAPA planning variable.

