#### Statistical analysis

A series of 3 (condition: control, intervention, and intervention with text message) × 2 (time: 6 and 12 weeks) mixed model multivariate analyses of covariance (MANCOVAs) with time as a repeated measures variable will be used examine the effects of the intention over time on study outcome variables. Baseline measures will be covariates in the model. A separate MANCOVA will be conducted for each set of dependent outcome variables: biomedical, behavioural and psychological. Pending significant multivariate effects, follow-up univariate analysis of covariance (ANCOVAs) will be used to identify differences for individual variables within each outcome set. Post-hoc follow-up tests will also be conducted to locate individual differences at the time intervals. Mediation analyses will be conducted by mediated multiple linear regression analysis with dummy-coded intervention conditions as the independent predictor variables, the constructs from the HAPA included as mediating variables, and the primary and secondary biomedical outcome variables as the dependent variables. Mediation will be confirmed through significant bootstrapped indirect effects using Preacher and Hayes’ [56] algorithms for multiple mediation and the PROCESS macro. Missing data will be handled by multiple imputation using regression analysis with the Markov-chain Monte Carlo (MCMC) estimation method. In addition, we will adopt a full intention-to-treat analysis with last measured data points carried forward in order to provide a conservative estimate of the effects.

Sample size has been determined by a power analysis using the G*Power 3.1 Program, suitable to evaluate differences between the three condition levels greater than 10%, with statistical power set at > 0.80 and alpha set at *p* < .05 [57]. A large effect size is assumed as previous studies that have used implementation intentions and reminder text messages [31], as well as studies using mental imagery and implementation intentions to increase exercise behaviour [58], have found large effect sizes. Given the estimated effect size, the total sample size required post-test is 66 and considering a potential 35% drop out rate and eliminations of cases due to missing data or spoilt questionnaires based on previous trials [21], we plan to recruit 102 participants at baseline or until the required sample size has been achieved.

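### The protocol expects HAPA constructs to mediate effects on behaviour as well as on biomedical outcomes, but the planned mediation analysis has only biomedical dependent variables

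*Protocol article*

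**What the plan says.** Under Assessments, Psychological measures, the protocol article gives the reason for measuring the HAPA variables: they are "psychological mediators that may explain the effects of the intervention on the behavioural and biomedical outcomes". Later in the same section it states what it expects for planning: "the if-then plan component of the intervention on the primary and secondary outcomes is expected to be mediated by the HAPA planning variable". The sentence before that one, on mental imagery, also refers to primary and secondary outcomes. Neither sentence is restricted to biomedical variables.

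The Methods/Design part of the abstract makes body weight the primary outcome. It lists among the secondary outcomes "behavioural (self-reported diet intake, and physical activity involvement) measures".

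The Statistical analysis section then specifies the mediation analysis. Dummy-coded conditions are the predictors. The mediators are described as "the constructs from the HAPA included as mediating variables". The outcomes of the model are given as "the primary and secondary biomedical outcome variables as the dependent variables". Indirect effects are to be bootstrapped. Behavioural outcomes appear elsewhere in that section only as one of the three sets analysed by condition and time: "A separate MANCOVA will be conducted for each set of dependent outcome variables: biomedical, behavioural and psychological".

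**The concern.** The stated mediation aim and the analysis meant to serve it cover different outcomes. HAPA, as the Background describes it under Changing health behaviour, is a theory of how behaviour comes about. It includes "a volitional phase that leads the individual to performing the actual behaviour". The link from construct to behaviour is therefore the one the theory speaks to most directly, and the planned mediation model leaves it out.

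If the plan is followed as written, the trial can report whether planning or self-efficacy carries an effect on weight, lipids or blood pressure. It cannot report whether they carry an effect on diet or exercise. If behavioural mediation models are added later without having been specified, the choice of outcomes will be open to the charge of having been made after the results were seen.

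**Working it through.** The point rests on comparing the text. No stated figure is in dispute.

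**Step 1. Outcomes covered by each statement**

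| Place in the protocol article | Outcomes to be explained by HAPA mediators | Diet and activity included? |
|---|---|---|
| Psychological measures, purpose | behavioural and biomedical | yes |
| Psychological measures, expected mediation | primary and secondary | yes, since the abstract lists them as secondary |
| Statistical analysis, mediation model | primary and secondary biomedical | no |

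The third row can be read with the word biomedical applying to both primary and secondary, or to secondary only. The primary outcome is body weight, so behaviour is excluded either way.

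**Step 2. Which links are planned**

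| Link | Planned? | Where |
|---|---|---|
| condition → HAPA construct | yes | psychological MANCOVA |
| condition → diet or activity | yes | behavioural MANCOVA |
| condition → HAPA construct → weight and other biomedical outcomes | yes | mediation model |
| condition → HAPA construct → diet or activity | no | nowhere |

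The behavioural MANCOVA gives the total effect of condition on behaviour. It contains no mediator and cannot supply the fourth row.

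**Step 3. Context figures.** The plan's sample size reproduces. For three groups, alpha 0.05 and an assumed f = 0.40 (the article says only that the effect is large), the smallest balanced total with power of at least 0.80 is 66, with power 0.818. Then 66 / (1 − 0.35) = 101.5, rounded up to 102. Adding dependent variables to the mediation model changes neither number.

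**Step 4. Illustration only.** The article gives no path sizes, so any power comparison rests on assumptions. The model used has 66 completers, 22 per arm:
- M = 0.8 × (either intervention arm) + e
- behaviour = b1 × M + e
- weight = b2 × behaviour + e

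All residuals have unit variance, so b1 and b2 are not standardised coefficients. The indirect effect is the arm-to-M coefficient times the M-to-outcome coefficient adjusted for arm. Power is the share of 95% percentile bootstrap intervals that exclude 0, per arm contrast.

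| b1 / b2 | Assumed reliability of behaviour | Power, behaviour | Power, weight |
|---|---|---|---|
| 0.3 / 0.3 | 1 | 48% | 9% |
| 0.4 / 0.4 | 1 | 68% | 16% |
| 0.5 / 0.4 | 1 | 75% | 23% |
| 0.5 / 0.5 | 1 | 74% | 32% |
| 0.5 / 0.5 | 0.5 | 55% | 30% |
| 0.5 / 0.5 | 0.3 | 38% | 32% |
| 0.5 / 0.8 | 0.5 | 51% | 52% |
| 0.5 / 0.8 | 0.3 | 37% | 51% |

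With about 500 simulated trials per row, the Monte Carlo standard error is at most √(0.5 × 0.5 / 500) = 0.022, or about 2 percentage points. When behaviour is measured without error, the model favours behaviour, because weight is one noisy step further on. With poor measurement the advantage shrinks, and with a strong behaviour-to-weight path it can vanish or reverse.

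**The case against.** The strongest reply is that the biomedical restriction is a defensible choice. Weight is the declared primary outcome and is measured on a scale. Diet and activity come from self-report diaries and questionnaires, and the Discussion itself warns of measurement error and affirmation bias. Regressing self-reported behaviour on self-reported mediators may produce an indirect effect that is partly shared response bias. This stands as a reason to keep weight as the primary mediation outcome and to read the behavioural models cautiously. It does not reconcile the sections, because the article gives no such reason and still states the wider aim.

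A reader might infer that the trial's behaviour-change mechanism goes wholly untested. The documents do not support that, since three of the four links in the second table are planned. A reader might also infer that a null indirect effect on weight would be reported as failure of the HAPA mechanism. Nothing in the article says so, and the two MANCOVAs would show any change in constructs and in behaviour.

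Nor does the account of HAPA under Changing health behaviour say that weight changes only through behaviour. The energy-balance statement is in the Background on overweight and obesity. The simulation's full-mediation structure is therefore an assumption, and its power gap is not evidence of harm.

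Two defences fail. The Present study section does call body weight change the key behavioural outcome, but the Biomedical outcomes section classes weight as biomedical, and the Discussion names diet and activity adherence as the key behavioural outcomes. Nor is this detail left to an unseen analysis plan: the article fixes the dependent variables explicitly.

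**Conclusion.** The inconsistency is real and narrow. The mediation aim covers behavioural outcomes and the only mediation analysis described does not, so one stated indirect path, from condition through a HAPA construct to diet or physical activity, has no planned estimate. This conclusion needs no numerical assumption.

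It concerns a secondary, explanatory analysis and leaves the primary comparison, sample size and data collection untouched. It is still worth correcting before analysis, because the mediating mechanism is central to the trial's rationale. The loss in power cannot be sized from the article. The illustrative gap ranges from large to none or reversed, depending on assumed path sizes and on how reliably behaviour is measured.

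**What to change.** In the Statistical analysis section, restate the dependent variables of the mediation analysis as the primary outcome and the secondary biomedical and behavioural outcome variables. Keep body weight as the primary mediation outcome, and label the behavioural models as secondary.

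The cost is a few more regressions on data already collected at baseline, 6 and 12 weeks. The number of added tests depends on which behavioural measures are named. The abstract's list implies two domains, diet and activity. Counting every instrument in the behavioural sections gives at least seven: the dietary screener (1), the eating-questionnaire domains (3), the food diary (1), the activity log (1) and the compliance items (1). Naming the measures in advance keeps this in bounds. The interpretation should note the extra secondary tests and the possibility of shared self-report bias between mediators and behaviour.

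If the sponsor does intend biomedical outcomes only, the sections can be reconciled the other way, by narrowing the aim in Psychological measures. That costs nothing but gives up the behavioural mediation question.

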### Hypotheses

The main hypothesis is that the intervention conditions adopting implementation intentions and mental imagery techniques, will result in statistically-significant independent improvements in the outcome measures relative to the control condition from the time of intervention and at 6 and 12 weeks. We also expect statistically-significant differences in the outcome variables across the two intervention conditions, such that the intervention condition with text messages leads to greater weight loss that the intervention condition alone.

It is also hypothesised that relative to baseline and week 6 and 12, the intervention with text message condition will lead to statistically-significant independent improvements on the biomedical, psychological, and behavioural outcome measures, compared with the intervention and control conditions. In particular, we expect to find statistically-significant differences in the key HAPA-based psychological mediators of the effects of the intervention components including planning (relevant to implementation intentions) and self-efficacy and motivation (relevant to mental imagery) over the same follow-up time points.

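### Mediation is to be confirmed by significant indirect effects in a family of about 144 to 288, with no deciding effect named and no adjustment stated

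*Protocol article*

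**What the plan says.** The Statistical analysis section plans multiple-mediator regressions with "dummy-coded intervention conditions as the independent predictor variables", and with "the constructs from the HAPA included as mediating variables, and the primary and secondary biomedical outcome variables as the dependent variables". The decision rule follows: "Mediation will be confirmed through significant bootstrapped indirect effects".

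The section does not say which mediator, contrast, outcome or follow-up decides, and it states no adjustment for these tests. Its one gating condition, a significant multivariate effect, is written for the univariate ANCOVAs and not for the mediation regressions.

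Three other places bear on the rule:

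- **Hypotheses** singles out "key HAPA-based psychological mediators of the effects of the intervention components including planning (relevant to implementation intentions) and self-efficacy and motivation".
- **Psychological measures** ties planning to the if-then component, and self-efficacy, motivation, outcome evaluation and intention to the imagery component. It does so for the primary and secondary outcomes alike. Of motivation it says that it "will be assessed at baseline by asking participants to respond to six items that question motivation".
- **Abstract, Methods/Design** lists the biomedical outcomes, and among the psychological ones "risk perception, outcome expectancy, intention, action self-efficacy, maintenance self-efficacy, goal setting and planning".

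**The concern.** Explaining how the programme works through the HAPA is a declared aim in the Background, Hypotheses and Discussion. A rule that attaches the word *confirmed* to whichever indirect effects prove significant, in a large family with no ranking, gives weak protection against a false account of the mechanism.

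The null that matters here is a plausible one. The session may raise planning and self-efficacy, as it is built to do, while those scales do nothing to weight or biomarkers over 12 weeks. The condition-to-mediator half of the product is then truly non-zero. Each indirect effect turns largely on a chance association between mediator and outcome, and there are many chances. A trial with no working HAPA pathway could then publish a confirmed one.

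**Working it through.** **The plan's own figures.** The article gives no error rate for the mediation rule, so only its sample size can be reproduced. A one-way comparison of three groups with f = 0.40 (the usual convention for the large effect that the article assumes) and alpha 0.05 has power 0.818 at N = 66 and 0.798 at N = 63. Allowing for 35% dropout, 66 / 0.65 = 101.5, rounded up to 102. Both stated numbers hold, and 66 completers (22 per arm) is used below.

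**Size of the family.**
- Contrasts: 3 arms give 2 dummies.
- Mediators: six HAPA scales in Psychological measures (risk perception, outcome expectancy, intention, action self-efficacy, maintenance self-efficacy, planning).
- Outcomes: body weight plus the 12 secondary biomedical variables in the abstract make 13, or 12 if body mass there means body weight.
- One follow-up: 2 × 6 × 13 = 156, or 2 × 6 × 12 = 144.
- Both follow-ups: body fat percentage and muscle mass come from DEXA, which is not done at week 6. So 2 × 6 × (13 + 11) = 288.
- With motivation as a seventh mediator, at one follow-up: 2 × 7 × 13 = 182.

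**Why simulation is needed.** The naive figure, 1 − 0.95^156 = 0.9997, does not apply. The indirect effect is a product a × b (condition to mediator, then mediator to outcome). Its bootstrap test is very conservative when both paths are zero, and the effects are correlated.

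**Set-up.** Three arms of 22, six mediators, 13 outcomes. Each outcome is regressed on both dummies and all six mediators. The indirect effect is a × b, with 1,000 bootstrap resamples and 800 simulated trials per setting. Correlations are 0.3–0.5 among mediators and 0.1–0.5 among outcomes. The event is at least one of the 156 intervals (95%) excluding zero. Unless noted, no mediator affects any outcome (b = 0).

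| Shift in HAPA scales, active arms v control | Percentile | Bias-corrected |
|---|---|---|
| None | 13–20% | 31–46% |
| 0.2 SD, all six | 23–33% | 44–60% |
| 0.5 SD, three of six* | 44–46% | not run |
| 0.5 SD, four of six* | 56–60% | not run |
| 0.5 SD, all six | 54–73% | 78–93% |
| 0.8 SD, three of six | 64–81% | 87–97% |
| 0.8 SD, all six | 84–95% | 96–99.5% |
| None, but b = 0.1–0.2 per mediator | 16–42% | 37–66% |

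*Separate run: 250 trials per setting, mediator correlation 0.4, outcomes correlated 0.4, or 0.3 with near-duplicate pairs such as weight and BMI. A shift of 0.3 SD in three or four scales gave 28–38%.

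Monte Carlo standard error near 50% is √(0.25/800) = 1.8 points, or √(0.25/250) = 3.2 points for the starred rows.

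The per-effect false-positive rate is about 0.2% (percentile) or 0.7% (bias-corrected) when nothing moves. It is 1.5–3.7% or 3.6–6.7% when three or all six scales shift by 0.5–0.8 SD. The number of effects drives the problem more than any one of them.

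**Does restricting the outcome suffice?** No. Body weight alone at one week (2 × 6 = 12 effects), unadjusted, still gives 11–25% (percentile) or 23–40% (bias-corrected) under those shifts.

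**With restriction and adjustment.** For weight only, both contrasts and percentile intervals, the false-confirmation rates at shifts of 0, 0.5 and 0.8 SD are:
- four mediators at 98.75%: 0.3%, 2% and 4%;
- three mediators at 98.3%: 0%, 2% and 5%.

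Bias-corrected intervals reach 6.5–9% at 0.8 SD.

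**The case against.** Mediation here is a secondary, explanatory analysis, and the comparison of weight between arms is untouched. Interval level and multiplicity for such analyses are often left to a statistical analysis plan, and none is shown. That stands: a missing adjustment alone would not be a finding. But the article does state a decision rule, and the point rests on that.

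Four stronger readings are tempting and are not supported:

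- **That the rule misfires in most trials whenever no construct mediates.** If the arms move no scale, there is no mediation either, and the rate is about 13–20% with percentile intervals. The highest figures need all six scales to shift by 0.5–0.8 SD. Table 1, Table 2 and the section on information for all participants count against this: risk perception and outcome expectancy are targeted by information that every arm receives. The large effect assumed for sample size is not a stated shift in HAPA scales.
- **That any single significant effect confirms the whole HAPA account.** The sentence does not say so and can be read effect by effect. The construct-to-component links in Psychological measures point the same way: an isolated path from risk perception to insulin would confirm none of them. Even so, each of 144–288 effects may be declared confirmed on its own.
- **That 156 is a minimum.** It is 144 if body mass duplicates body weight.
- **That effects showing harm would count as confirmation.** The Hypotheses section predicts improvements, and a positive indirect effect is not always a worsening: a rise in HDL or muscle mass is not. What remains is that the mediation rule does not itself carry the direction.

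**Conclusion.** The concern holds in limited form. The article promises confirmation from about 144–288 indirect effects without saying which ones decide. Where the session shifts the HAPA scales but they have no effect on the outcomes, a realistic reading of the design (three or four scales moved by 0.5 SD) puts the chance of at least one false confirmation near 45–60%. If all six scales move by 0.5–0.8 SD it is 54–95%.

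These figures assume 95% percentile intervals, 66 completers, one follow-up, 13 outcomes and the correlations listed. None of the shifts or correlations is in the article, so the figures show scale and do not predict a rate. The change should be made: the mechanistic claim is a stated aim and is not credible under the rule as written. The primary efficacy result does not depend on it.

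**What to change.** Reword the mediation sentences in Statistical analysis:

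1. Make body weight at week 12 the single confirmatory mediation outcome.
2. Name the confirmatory mediators from Hypotheses: planning, action self-efficacy and maintenance self-efficacy. Add motivation only if it is also measured after the intervention. Hypotheses treats it as a mediator and Psychological measures describes it as assessed at baseline, so the two must be reconciled first.
3. Name the contrast or contrasts that decide.
4. Require the indirect effect to be in the hypothesised direction (weight reduction).
5. Specify percentile bootstrap intervals at level 1 − 0.05/k, where k is the number of confirmatory effects. Three mediators and one contrast give 98.3%; four and one give 98.75%; three and two contrasts (k = 6) give 99.2%. The adjusted runs above divided by the number of mediators only while counting both contrasts, so dividing by all k effects is stricter.
6. Report every other indirect effect as an exploratory estimate with its interval, and do not call it confirmed.

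If the sponsor prefers not to name a family, the alternative is to label the whole mediation analysis exploratory.

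The cost is text only: no new data and no extra participants. The named effects get somewhat wider intervals, and the remaining pairs lose any confirmatory claim. That includes intention and outcome evaluation, which Psychological measures also expects to mediate. They could join the family at the price of a larger k.
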